### Ethical considerations

The Northwest Permanente Prediction Model Governance Committee reviewed and approved implementation of the model in KPNW. The Kaiser Permanente Interregional Institutional Review Board (IRB) has reviewed and approved the study protocol and will review any subsequent amendments. All sites have ceded authority to the IRB for ongoing monitoring of the research aspects of the project. A waiver of informed consent was granted as the sample size makes consenting individuals impractical and only secondary data will be used for the effectiveness analyses. The waiver allows sites access to identifying information at the local level; however the data will be anonymized prior to the pooled analysis. Clinicians will be sent a study information sheet prior to recruitment for the implementation surveys; it will be made clear to them that by submitting a survey they are consenting to participate in the study. All EHR and claims data from the three participating sites will be stored locally. Only de-identified datasets will be shared between sites under appropriate data use, sharing, and transfer compliance agreements. All project staff who work on research projects and handle human subjects’ data or have human subjects contact, sign confidentiality agreements and receive IRB and HIPAA training/certification.

We will convene an independent Data and Safety Monitoring Board (DSMB) composed of a Chair and at least two members; the chair and at least one member will have extensive expertise in suicide prevention in health care settings, at least one member will have statistical expertise in stepped-wedge design and pragmatic trials. The DSMB will create a charter, maintained by the Chair, and will meet twice annually during the study to discuss recruitment progress and any reported safety concerns. Interim analyses for the DSMB meeting will include patient characteristics by implementation phase and wave for all sites and a quarterly count of individuals with a suicide attempt within 90 days of a visit and 180 days of follow up across all sites. The latter allows for surveillance of safety by looking at overall patterns of suicide attempts without examining the main outcome prior to the formal study analyses. The DSMB will have access to interim results to make decisions regarding premature termination of the trial. The site project managers will also solicit from clinic champions and report adverse events or unintended consequences of the trial or trial conduct, and these will be presented to the DSMB.

### Creation of an implementation tool kit

The process evaluation for the study will culminate in an implementation tool kit for health care leaders considering adoption of suicide risk models. The tool kit will include summaries of the findings from the preliminary [35, 37, 38] and current studies; the ethical framework to guide implementation decision making [36]; guidance for consideration in selecting risk thresholds for action based on clinical learnings that emerge during implementation; detailed contextual descriptions of implementing sites (e.g., setting, resources, existing suicide prevention care model and infrastructure supports) as case examples; descriptions of local determinants (e.g., barriers and facilitators) and whether and how much they were modified by the implementation strategies over time; descriptions of implementation strategies and plans that were considered and executed, including adaptations and reasons for adaptations; the final IRLMs for each site; training materials and resources; and estimated staffing allocations necessary for key roles (e.g., clinic champions, programmers, etc.).

### Dissemination of study results

Early and ongoing implementation findings and eventually trial results will be communicated to the participating sites through the clinical champions and implementation teams and will be included in a revised tool kit. Study results will further be communicated through manuscripts in peer-reviewed journals, national conferences, and through several networks that study investigators routinely collaborate with (e.g., Mental Health Research Network, Kaiser Permanente National Suicide Learning Collaborative, Suicide Prevention Resource Center, Zero Suicide International). Consistent with our values of collaboration and transparency, we will make our documentation, research methods, protocol, publicly available data collection tools and, upon completion of analyses and publications, a de-identified dataset (redacted to prevent re-identification) available upon request to interested researchers for non-commercial research use.

### Potential study limitations

This study will be conducted in integrated health care systems and findings may not generalize to other settings. Assessment of suicide attempts using EHR and claims data will reduce bias associated with patient report but may miss suicide attempts for patients who do not seek care following a suicide attempt if the attempt is not later recorded in the EHR or their attempt is not discoverable in the EHR. The study will identify at-risk patients who present for behavioral health visits but will not identify patients who are not engaged in these services nor patients who only present for care in other settings, such as primary care clinics or behavioral health clinics external to the three participating health care systems. Finally, the proposed stepped wedge study design is not as methodologically rigorous as a true cluster-randomized design, but this design was chosen in partnership with health system leaders, who did not want to delay implementation across behavioral health clinics longer than necessary.

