### Proposed care models (mechanisms of action)

Figure 3 shows a standard suicide prevention care model (usual care) and the proposed enhanced care suicide risk model (intervention). A typical workflow that involves suicide risk identification, when a patient presents for a behavioral health visit, may begin with suicide risk screening (typically the PHQ9 [42] in the participating sites). If the PHQ9 is missed, refused, or if item 9 (“Over the last two weeks, how often have you been bothered by thoughts that you would be better off dead or of hurting yourself in some way?”) is denied, the workflow may terminate, however a clinician could also proceed if clinically indicated. Potentially terminal processes are indicated by a dark background in Fig. 3, text boxes with white backgrounds indicate continuation of the workflow. The expectation is that when patients respond positively to item 9 (i.e., respond with a score of 2 “more than half the days” or 3 “nearly every day”), a comprehensive suicide risk assessment is conducted (typically the Columbia Suicide Severity Rating Scale [C-SSRS] [43] in the participating sites). Again, if the risk assessment is missed, refused, or if risk is denied the workflow may terminate. The expectation is that when risk is confirmed, depending on acuity, a referral is made to outpatient supportive services or to the emergency department or inpatient setting.

The enhanced care suicide risk model (intervention) demonstrates the proposed changes in workflow with the risk model implementation. In this model, the suicide risk model flags the clinician in the EHR to conduct additional suicide risk screening. The expectation is that if the PHQ9 were missed, refused, or if item 9 was denied in the presence of a model-generated risk flag indicating elevated estimated risk, then the clinician would proceed to the C-SSRS as if the screening were positive.

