### Data sources

Primary and secondary outcomes will be derived from EHR and administrative claims data. As members of the MHRN, all participating health systems have complete capture of EHR and claims data for their patients [14]. Additionally, all MHRN sites have structured their electronic health records and insurance claims data into locally maintained federated data systems known as the Virtual Data Warehouse (VDW) [45] at each site to support comprehensive and efficient capture of health care encounters, diagnoses, medications, patient-reported outcomes, demographics and other administrative and clinical data. We will leverage these data sources and previously validated MHRN definitions [46] for measurement of our variables. Implementation outcomes will be derived from meeting minutes, observations, field reports, and survey data collected from clinicians in participating clinics.

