### Study measures and effectiveness outcomes

The primary outcome measure is fatal or non-fatal suicide attempt (binary yes/no) within 90 or 180 days of a behavioral health visit as measured using diagnosis codes for intentional self-harm (International Statistical Classification of Diseases and Related Health Problems, Tenth Revision [ICD-10] codes X60-X84; Y87.0). Suicide deaths will be ascertained from government mortality records. The denominator will be the total number of visits to behavioral health clinics and the numerator will be reported as the number of suicide attempts per 1000 visits. In addition to the primary outcome, we will examine proximal outcomes and crisis utilization measures. Proximal outcomes include measures of engagement with services documented in the EHR within the observation period. These are defined as: evidence-based suicide prevention interventions (safety planning, lethal means counseling, or caring contacts) on or after the risk identification (index) encounter, an outpatient encounter (includes telephone, virtual, and office visits) by a behavioral health clinician or psychiatrist subsequent to the index encounter, any contact with behavioral health within seven or 14 days of the index visit (includes phone calls, letters, patient portal messages, or other caring contacts in addition to encounters described above), frequency of contacts, latency to next encounter after index, and persistence in psychotherapy defined as no gap in psychotherapy visits > 90 days during the observation period. Crisis utilization measures include any encounters in the emergency department or inpatient stays subsequent to the index encounter within 90 days and 180 days.

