These models will also be used to test mediators/mechanisms, given that we hypothesize that identification alone will not reduce suicide outcomes but rather increase the number of people receiving suicide intervention, which could lead to improvement (i.e., decrease) in suicide outcomes. Mechanisms include interaction with the alert and initiation of assessment, which starts the outpatient care pathway. We will also stratify analyses by health system site, and test for mental health diagnoses and prior suicide attempts as moderators. Importantly, we will exclude ‘training’ months for each phase of clinic implementation from the main analyses, since clinicians and patients may be partially exposed as the models are implemented and clinicians trained. In a secondary set of analyses, we will explore potential heterogeneity in treatment effects between clinics. Here we will conduct additional analyses to test within cluster comparisons of exposed and unexposed periods.

To examine the effectiveness of a suicide risk model on health service engagement and suicide attempt outcomes, we will start with similar descriptive and GLMMs analyses proposed previously for identification and recognition. The analyses here will focus on each unique health service engagement (supportive and crisis encounters separately) and suicide attempt outcomes, stratified by exposed (intervention) versus unexposed (control) groups. Suicide attempts will be captured by health system records using ICD-10 diagnosis codes occurring within the same 90-day and 180-day time periods. We will also use a Kaplan-Meier method and Cox-proportional hazards models to examine time-to-event for health service engagement and suicide attempts, with statistical adjustment for clinical and demographic factors. Individuals will be censored at the time of death or at 180 days past the index visit. We will again add terms for calendar month as well as site to account for variation by season and health system.

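### Recording of non-fatal suicide attempts may be more complete in intervention than in control periods, and the article neither says so nor offers a check on it

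*Protocol article*

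**What the plan says.** Under Study measures and effectiveness outcomes, the primary outcome is a fatal or non-fatal attempt within 90 or 180 days of a behavioral health visit, "as measured using diagnosis codes for intentional self-harm" (X60-X84; Y87.0). For the fatal part the same section adds: "Suicide deaths will be ascertained from government mortality records". The Analysis plan for effectiveness outcomes repeats the coding rule: "Suicide attempts will be captured by health system records using ICD-10 diagnosis codes". Neither section restricts the encounter at which a code may be entered. Data sources states that "all participating health systems have complete capture of EHR and claims data for their patients".

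Potential study limitations says of the data source: "Assessment of suicide attempts using EHR and claims data will reduce bias associated with patient report". It goes on to say that the source "may miss suicide attempts for patients who do not seek care following a suicide attempt if the attempt is not later recorded in the EHR". It does not mention whether that chance of later recording could differ between control and intervention periods.

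Proposed care models describes what changes under the intervention. When the PHQ9 is missed or refused, or item 9 is denied, and the model has raised a flag, "the clinician would proceed to the C-SSRS as if the screening were positive". Objectives and hypotheses adds the expectation that referrals to outpatient supportive services, and their receipt, will rise.

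**The concern.** By the article's own account, whether an attempt without immediate care enters the outcome depends on later contact and documentation. Assessment and contact are what the intervention is designed to increase among flagged patients. If it works as hypothesized, a non-fatal attempt that would go unrecorded in usual care has more chances to be disclosed and coded after crossover. The recorded attempt rate could then stay level while the true rate falls.

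A null or adverse primary result would therefore have two explanations, no benefit or better recording, and nothing stated in the article helps to separate them. This matters because the Conclusion says the trial will settle whether the risk model reduces attempts relative to usual care.

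**Working it through.** **Inputs from the article**

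- Anticipated attempt rate: 0.6% within 90 days of a visit, n = 2,370 (Sample size and power analysis). Check: 395,000 × 0.006 = 2,370, which agrees. No stated figure is in dispute here.
- Share of patients flagged: 4–5% (same section).
- C-statistics of the MHRN models: 0.83 to 0.86 (Background).
- Coding sensitivity in either period: not given. All sensitivities below are assumptions.

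**Formula**

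Observed RR = true RR × [F + (1 − F) × (1 + w × (s1/s0 − 1))]

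- F: share of recorded events that are fatal, and so unaffected by coding.
- w: share of non-fatal attempts that occur in patients who get extra contact.
- s0, s1: coding sensitivity in control and intervention periods.

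**What w might be**

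If flagged patients carried only their population share of attempts, w would be about 0.05. A model that discriminates at 0.83–0.86 concentrates attempts among those flagged. As an illustration, assume equal-variance normal scores, so that the separation is d = √2 × Φ⁻¹(C). This gives d = 1.35 for C = 0.83 and d = 1.53 for C = 0.86. Choose the cut-off t that flags a share f in total: 0.006 × P(Z > t − d) + 0.994 × P(Z > t) = f. Then w = P(Z > t − d).

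- C = 0.83, f = 0.04: w = 0.34
- C = 0.86, f = 0.05: w = 0.44

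These values depend on the normal model and on the published discrimination carrying over to these clinics.

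**Observed RR when the true RR is 0.90 and F = 0**

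| s0 → s1 | w = 0.05 | w = 0.34 | w = 0.44 | w = 1 |
|---|---|---|---|---|
| equal | 0.90 | 0.90 | 0.90 | 0.90 |
| 0.80 → 0.84 | 0.902 | 0.915 | 0.920 | 0.945 |
| 0.80 → 0.88 | 0.904 | 0.931 | 0.940 | 0.990 |
| 0.70 → 0.84 | 0.909 | 0.961 | 0.979 | 1.08 |

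Example: 0.90 × (1 + 0.44 × (0.84/0.70 − 1)) = 0.90 × 1.088 = 0.979.

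With F = 0.10 the last row becomes 0.908, 0.955, 0.971 and 1.06. Deaths from mortality records dampen the distortion but do not remove it. In this grid a true benefit appears as harm only when every non-fatal attempt is affected and sensitivity rises from 0.70 to 0.84.

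**Does anything stated already remedy it?**

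- The models for identification and recognition adjust for visit frequency during follow-up, and similar models are planned for attempts. Visit frequency is measured after exposure and may itself be changed by the intervention. The article elsewhere treats service engagement as a mediator, so adjusting for contact could remove part of the real effect along with any recording bias.
- Complete capture of EHR and claims covers encounters that took place. It does not cover attempts never disclosed at one.

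**The case against.** The strongest case on the other side has five parts.

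- **Codes are not the only measure.** A reader might infer that the whole primary outcome rests on health-record codes. It does not: deaths come from mortality records, and claims supplement the EHR. This stands, and the point is limited to non-fatal attempts.
- **Direction is not shown.** A reader might infer that the comparison is known to be biased against the intervention. The documents do not support that. Nothing says that an attempt disclosed on a C-SSRS produces a self-harm code. Usual care already screens and assesses at all three systems. More visits would enlarge the all-visits denominator and could lower the rate per 1000 visits. Fewer crisis encounters could reduce coding. All of this stands. Masking of benefit is the likelier direction, but it is not established.
- **The article does not claim that missed attempts are non-differential.** This is correct. The limitations section is silent on the question, and its statement about patient-report bias is not itself wrong.
- **Supportive analyses may sit in an SAP not shown.** This is fair, so the absence of such an analysis from the article is not counted as an omission. What remains is that the article takes a position on bias in its outcome source, concedes dependence on later recording, and leaves out that the intervention acts on that same step.
- **Emergency and inpatient codes also depend on the intervention.** Proposed care models sends some confirmed risk to those settings, depending on acuity. This stands. Such codes are less dependent on behavioral health contact, not independent of it.

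**Conclusion.** The point holds in limited form. Ascertainment of non-fatal attempts may differ by exposure period, through a mechanism that follows from the article's own description of its outcome and its intervention. The article does not acknowledge this, and the visit-frequency covariate is not a clean remedy. The probable effect is to mask benefit.

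Its size is unknown. For a true RR of 0.90, the assumed scenarios run from no distortion to an observed 1.08. They run from 0.915 to 0.98 if flagged patients carry 34–44% of attempts and sensitivity is higher in intervention periods by the amounts tabulated. Every sensitivity value is an assumption, so these figures show what could happen and do not estimate what will. The stronger conclusion, that the primary comparison is demonstrably biased against the intervention by a stated percentage, is not supported.

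**What to change.** 1. Keep the primary outcome as stated.
2. Pre-specify a supportive analysis that uses the primary model but counts only self-harm codes first recorded at an emergency or inpatient encounter, plus suicide deaths from mortality records. Describe these events as less dependent on behavioral health contact, not independent of it.
3. Add a sentence to Potential study limitations saying that recording of non-fatal attempts may differ between control and intervention periods.
4. State in advance how the two results will be read together. A difference is consistent with differential ascertainment but does not prove it, because an effect confined to less severe attempts, or increased emergency referral under the intervention, could produce the same gap.

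The cost is small. Emergency and inpatient encounters are already planned as crisis utilization measures, and deaths are already to be ascertained, so this is one further model run on data in hand. The downside is fewer events, and so a less precise estimate, in the supportive analysis.

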## Conclusion

Few suicide risk models derived from administrative and clinical data have been tested in real world care settings. This trial will determine whether the use of such a risk model reduces suicide attempts compared to usual care. By describing important implementation factors, use of such risk models, if effective, may be accelerated for other health care systems.

## Data Availability

No datasets were generated or analysed during the current study.

## Abbreviations

C-SSRS: Columbia-Suicide Severity Rating Scale
CBT: Cognitive Behavioral Therapy
CFIR: Consolidated Framework for Implementation Research
DSMB: Data and Safety Monitoring Board
HER: Electronic Health Record
EPIS: Exploration, Preparation, Implementation, and Sustainment
GLMMs: Generalized Linear Mixed Models
HFH: Henry Ford Health
HIPAA: Health Insurance Portability and Accountability Act
HP: HealthPartners
ICD-10: International Statistical Classification of Diseases and Related Health Problems, Tenth Revision
IRB: Institutional Review Board
IRLM: Implementation Research Logic Model
MHRN: Mental Health Research Network
NSSP: National Strategy for Suicide Prevention
OR: Odds Ratio
ORIC: Organizational Readiness to Change
PHQ9: Patient Health Questionnaire-9
RR: Relative Risk
SUS: System Usability Scale
US: United States
VDW: Virtual Data Warehouse
ZS: Zero Suicide
